**Fig. 1 Fig1:**
[figure not shown]
Study Flow Diagram

Our intervention will be administered to patients at their usual pharmacy after consent is obtained. The intervention involves six main strategies in addition to the COPD education pamphlet (see Additional file 6); (1) medication review, (2) patient education, (3) a written COPD Action plan provided in collaboration with their family physician (see Additional file 7), (4) patient referral to pulmonary rehabilitation in collaboration with their family physician, (5) provision of, or referral to, smoking cessation counseling (where applicable), and (6) referral to a community-based chronic disease self-management program.Medication reviewPatients will have a thorough review of their current COPD medications. The review will consist of current medications, doses, dosage forms, duration and timelines of therapy, appropriateness of therapy, and patient expectations. Drug-related problems will be identified and recorded, and recommendations for their resolution will be forwarded to the patient’s primary health care providerPatient educationThe education will consist of evaluating current inhaler technique and the subsequent correction or teaching where required. Pharmacists will also deliver adherence support strategies by determining knowledge deficits, understanding the patient’s expectations of their COPD therapy, and focusing on teaching about medications and administration techniques. The “teach-back technique” will be used [26–28]COPD Action PlanA written “COPD Action plan” Form will be provided and explained to the patient. This action plan will inform the patient how to proceed when COPD symptoms worsen. This action plan will be developed in conjunction with the patient’s physician, where patients do not already have a standing prescription for antibiotics and oral steroids. The form is divided into two sections, each section having three subcategories. These include: (1) “My Symptoms” (I feel well, I feel worse, I feel much worse) and (2) “My Actions” (stay well, take action, call for help). This action plan is easy to read and simple to follow [29]. A copy of this will be provided to the patient and to the patient’s physician (faxed). When needed, a prescription suggestion for antibiotics and oral steroids will be provided to the physician for signature and fax back to the pharmacy, to facilitate the action planPulmonary RehabilitationIn NL, access to specialized personnel or services is usually achieved through referral by the family practitioner. As such, all patients will have a request for referral to pulmonary rehabilitation sent to their family physicianSmoking cessationPharmacists will also refer current smokers to smoking cessation services, or offer smoking cessation counseling within the pharmacy, where availableCommunity-based chronic disease self-management programPharmacists will refer all patients to the community-based chronic disease self-management program, “Improving Health My Way.”Patients attending pharmacies assigned to the control group will receive a pamphlet on COPD and usual care according to the clinical judgment of the participating pharmacist. Care will not be limited or directed by the study team in any way. Patients will be able to withdraw from the study at any time. Research staff will be available to participating pharmacists to answer questions or provide support as necessary.

### Participant timeline

Patients will be recruited over a 12-month period between May 2016 and May 2017 and will be followed for 6 months. See Fig. 1 for an overview of the participant process.

### Sample size calculation

We based our sample size calculation on our primary outcome of change in adherence measured using the MPR. We assumed a baseline adherence of 50 % [16, 38], a minimal detectable difference of a 14 % absolute change, a standard deviation of 30 %, a correlation of 0.6 between baseline and follow-up measurement, a type 1 error rate of 5 %, a type 2 error rate of 20 %, and an intraclass correlation coefficient of 0.05 [39]. We corrected for correlation amongst patients within clusters using the inflation factor 1 + *p*(*m* − 1) where *m* is the mean number of observations per cluster and *p* is the intraclass correlation. We estimated that approximately 140 patients within at least 20 clusters would need to be enrolled to detect a 14 % change in adherence with 80 % power. We will maintain a cluster size of 20 pharmacies (10 intervention and 10 control) and aim to enroll seven patients per pharmacy, or 140 patients in total. The sample size for our study will, therefore, have 80 % power to detect a minimum difference of a 14 % change between the intervention and control groups.

### Recruitment

Pharmacists will be recruited primarily via email through the provincial pharmacy associations, with follow-up email and mail requests as needed. Patients presenting with a new prescription or refill for COPD medications will be approached by the pharmacist to gauge their interest in participating in the study.

We will provide ongoing support and work closely with pharmacies to ensure that recruitment targets are appropriate for the community they serve. Moreover, we will aim to monitor the recruitment process through regular communication via site visits, telephone calls, and emails to discuss any issues or challenges that might arise.

### Randomization

Randomization will be at the level of the community pharmacy. A random number list will be generated using Excel 2013 (Microsoft Corporation) and pharmacies will be assigned to either intervention or control in a 1:1 ratio by the research assistant as they are recruited.

### Blinding

It will not be possible for participating pharmacies to be blinded to which group they are assigned due to the nature of the intervention. The data analyst will be blinded to treatment assignment.

### Data collection methods

Pertinent demographic and contact information for participating pharmacies will be recorded. Patient study data will be collected using Data Collection Forms after pharmacists obtain their consent. Follow-up will last for 6 months after enrollment and the delivery of the intervention or usual care. All information will be stored at the pharmacy. The research assistant will collect the information in hardcopy or by fax for data entry. A blinded data analyst will conduct the final analysis.

Data collected will include: basic contact information (name, mailing address, email, and phone/cell number) as well as information related to the outcomes of the study, including questionnaires and prescription and health care resource utilization information. The Data Collection Forms are to be completed by the patient and pharmacist at baseline and 6 months. The research assistant will be available to assist in the completion of Data Collection Forms at the request of the pharmacist. Any harms reported by the participants will be recorded and included in the final manuscript.

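### Harms rest on participant report at unblinded pharmacies while only the intervention arm has a study-driven medication review, so harms may be detected unequally between arms

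*Protocol article*

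**What the plan says.** The Data collection methods section of the protocol article states the harms rule in one sentence: "Any harms reported by the participants will be recorded and included in the final manuscript". The wording is the same for both arms. On timing, the section says: "The Data Collection Forms are to be completed by the patient and pharmacist at baseline and 6 months". Its list of what is collected names contact details, questionnaires, prescription information and health care use. Harms are not in that list, and the content of the forms is not shown.

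The Interventions section sets out different contacts by arm. In the intervention arm the pharmacist reviews the patient's COPD medications and explores expectations and gaps in knowledge. Of that review it says: "Drug-related problems will be identified and recorded, and recommendations for their resolution will be forwarded" to the primary care provider. The same arm receives a written action plan, developed with the physician "where patients do not already have a standing prescription for antibiotics and oral steroids". For that plan: "When needed, a prescription suggestion for antibiotics and oral steroids will be provided to the physician for signature and fax back to the pharmacy". Control patients "will receive a pamphlet on COPD and usual care according to the clinical judgment of the participating pharmacist", and for them the article adds: "Care will not be limited or directed by the study team in any way".

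The Blinding section says that pharmacies cannot be blinded and that the data analyst will be. The Outcomes section lists, as patient-reported secondary outcomes at 6 months, use of antibiotics and oral corticosteroids for exacerbations and counts of physician, hospital, emergency and pharmacy visits. The Statistical methods section plans between-group analysis of the primary and secondary outcomes. Harms are neither.

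**The concern.** The harms rule depends on what patients say, and the study gives the two arms different occasions to say it. A medication review is a conversation about medicines, and a patient who has a side effect is likely to mention it there. In the control arm no such conversation is part of the study. The person hearing and recording the report knows the allocation, and a blinded analyst cannot repair unequal detection further upstream.

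Two consequences follow. First, a side effect voiced at the baseline review fits the wording of the harms rule although the intervention could not yet have caused it. Second, the action plan raises a foreseeable safety question about courses of antibiotics and oral steroids. The article counts use of these drugs in both arms but describes no question on their adverse effects. Harms published from a two-arm trial will be read by arm, with or without a test. An excess in the intervention arm could then reflect opportunity to report rather than harm.

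**Working it through.** The plan gives no figure on this point, so there is none to reproduce. The check is a comparison of sections, followed by an illustration of scale.

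**Step 1. Opportunity for a harm to surface, by arm**

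| Element | Intervention | Control | Section |
|---|---|---|---|
| Harms rule | participant report | participant report | Data collection methods |
| Forms at baseline and 6 months | yes | yes | Data collection methods |
| Study-driven medication review, with problems recorded | yes | no | Interventions |
| Pharmacy blinded | no | no | Blinding |
| Antibiotic and oral steroid use; hospital, emergency and physician visits | collected | collected | Outcomes |
| Question on side effects of medicines or of those courses | none described | none described | Data collection methods, Outcomes |

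The third row is the asymmetry: the rule is identical, but the occasion to report is not. The fifth row shows that part of the safety information is already collected equally. The last row shows what remains uncovered.

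**Step 2. Illustration of scale**

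Input from the Sample size calculation section: 140 patients in 20 pharmacies, 10 per arm with 7 patients each, so 70 per arm. The true proportion with a harm (the same in both arms) and the detection probabilities are assumptions; the article gives neither.

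Expected number recorded = 70 × true proportion × detection probability.

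With equal true proportions, the apparent ratio = detection in intervention / detection in control. The true proportion cancels, so the ratio only restates the assumed detection rates.

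| True proportion, both arms | Detection, control | Detection, intervention | Recorded, control | Recorded, intervention | Apparent ratio |
|---|---|---|---|---|---|
| 20 % | 50 % | 50 % | 7.0 (10 %) | 7.0 (10 %) | 1.0 |
| 20 % | 50 % | 70 % | 7.0 (10 %) | 9.8 (14 %) | 1.4 |
| 20 % | 50 % | 90 % | 7.0 (10 %) | 12.6 (18 %) | 1.8 |
| 20 % | 30 % | 90 % | 4.2 (6 %) | 12.6 (18 %) | 3.0 |
| 10 % | 50 % | 70 % | 3.5 (5 %) | 4.9 (7 %) | 1.4 |
| 30 % | 50 % | 90 % | 10.5 (15 %) | 18.9 (27 %) | 1.8 |

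Example: 70 × 0.20 × 0.50 = 7.0 and 70 × 0.20 × 0.90 = 12.6; 12.6 / 7.0 = 1.8.

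Equal detection gives no spurious difference. Better detection in the intervention arm gives a spurious excess there. Whether detection will in fact differ, and by how much, cannot be derived from the article.

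**The case against.** The strongest reply is that the text does not establish a bias. Several readings that a reader might infer go further than the article does:

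- **That the trial will publish a biased harms comparison.** Harms are only to be recorded and included in the manuscript. No test of harms between arms is planned.
- **That problems found at the medication review count as harms.** The article places them in the review, as matters passed to the primary care provider. It takes harms from a different source, the participants. Nothing merges the two. But nothing keeps them apart either when a patient mentions a side effect during the review.
- **That reporting is wholly unprompted.** The forms are completed in both arms at the same times and are not shown, so the 6-month form may already ask about harms. A condensed article may also leave the wording of such a question to the full protocol.
- **That only the intervention arm is supplied with standby antibiotics and steroids.** The text describes a suggestion for physician signature, when needed, where no standing prescription exists. Control care is unrestricted, so control patients may hold the same prescriptions.
- **That the courses go unrecorded.** Their use for exacerbations, and acute care contacts, are secondary outcomes in both arms.
- **That more harm from more courses would be bias.** It would be a true effect of the intervention. It is a reason to ask both arms alike, not evidence of unequal detection.

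All of this stands, and it limits the point to a risk. It does not remove it. The stated rule fixes participant report as the source and commits to publication, and the study-driven occasion to report exists in one unblinded arm only. Counts of drug use and visits replace a question on side effects only in part.

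**Conclusion.** The point holds as a risk of unequal detection. It rests on three statements in the article: harms come from participant report, pharmacies are unblinded, and a medication review is a study procedure in the intervention arm alone. The expected direction is to make the intervention look worse in the published harms. The article does not allow the size to be estimated. The ratios of 1.4 to 3.0 show only what assumed detection rates would produce with no true difference, and must not be read as a forecast.

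The article does not support saying that the harms data are biased or cannot be interpreted. Harms are not a primary or secondary outcome, and the adherence analysis is unaffected. If the 6-month form already puts the same harms question to both arms, most of the concern falls away once the article says so. This is a cheap improvement to a loosely worded rule, not a flaw that threatens the trial's main conclusion.

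**What to change.** Replace the harms sentence in Data collection methods with a rule on these lines:

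1. At the 6-month contact, pharmacists in both arms ask the same scripted question on the existing Data Collection Form. It covers side effects or problems with medicines since enrolment, including with any antibiotic or oral steroid course.
2. Any presentation of harms by arm uses these answers only.
3. Drug-related problems found at the baseline medication review are tabulated separately, as process data on the intervention.

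Physician, emergency and hospital visits need no new question because they are already collected at 6 months.

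The cost is one item on a form that patient and pharmacist already complete: about a minute more per patient, and more minor symptoms recorded in both arms. Treatment, sample size and primary analysis do not change. The information cannot be collected in the same way once a patient's 6-month contact has passed. Recruitment began in May 2016, so the first of these contacts falls about November 2016. If the form already holds such a question, stating it in this section, together with items 2 and 3, is enough.

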### Data management

Patient information will be coded using unique numerical identifiers assigned by the research staff. All data entered electronically will be identified only by this code, and the master list will be kept in a locked cabinet in the locked office of the principal investigator. All electronic information will be kept in an encrypted file.

### Statistical methods

Baseline characteristics will be compared between the intervention and control groups at the pharmacy (cluster level) and patient level to assess for possible cluster imbalances. Differences in the primary and secondary outcomes of interest between the intervention and control groups will be measured at 6 months using the individual as the unit of analysis. Generalized linear mixed models will be used to account for the clustering effect at the pharmacy level. We will assume an exchangeable correlation structure, calculate robust standard errors, and specify the appropriate outcome distribution and link function for each model (e.g., binomial distribution and logit link function for dichotomous variables and a Gaussian distribution and identify link function for continuous variables). In addition to an unadjusted analysis, we will conduct a secondary analysis to adjust for potential differences in multiple baseline covariates at both the pharmacy level (e.g., pharmacy type, location, prescription volume, pharmacist to technician ratio) and the patient level (e.g., age, sex, baseline medication knowledge, baseline adherence, baseline inhaler technique). Standard model diagnostics will be conducted to check for model assumptions. All analysis will be intention-to-treat. Multiple imputation will be used to account for missing data.

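### Robust standard errors are prescribed for 20 pharmacies with no small-sample correction; in their ordinary form they make the nominal 5 % test of a continuous outcome run at about 8 %

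*Protocol article*

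**What the plan says.** The Statistical methods section of the protocol article states the model and the variance estimator for the primary and secondary outcomes together: "Generalized linear mixed models will be used to account for the clustering effect at the pharmacy level", followed by "We will assume an exchangeable correlation structure, calculate robust standard errors, and specify the appropriate outcome distribution". A secondary analysis then adjusts for patient-level and pharmacy-level covariates. The pharmacy-level ones given as examples are "pharmacy type, location, prescription volume, pharmacist to technician ratio".

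The number of clusters is set in the Sample size calculation: "We will maintain a cluster size of 20 pharmacies (10 intervention and 10 control) and aim to enroll seven patients per pharmacy, or 140 patients". The error rates and intraclass correlation there are "a type 1 error rate of 5 %, a type 2 error rate of 20 %, and an intraclass correlation coefficient of 0.05". The article names no small-sample correction to the robust errors and no reference distribution for the tests.

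**The concern.** Sandwich standard errors are justified by a large number of independent clusters. With 10 pharmacies per arm the ordinary form is biased downward, and a normal reference ignores the imprecision of the variance estimate. Both errors act in the same direction: intervals too narrow and p-values too small. Each pharmacy-level covariate uses up one of the few cluster-level degrees of freedom, so the adjusted model suffers more.

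At stake is the 5 % type 1 error on which the superiority claim and the sample size rest. The article goes beyond leaving the estimator open: it names one whose ordinary form does not deliver 5 % at this number of clusters.

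A lesser matter is the wording. A mixed model is a random-effects method, whereas an exchangeable structure with robust errors most naturally describes generalized estimating equations (GEE). For the logit models the two estimate different odds ratios (cluster-specific and population-averaged).

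**Working it through.** **Inputs from the Sample size calculation.** 20 pharmacies (10 + 10), 7 patients each, ICC 0.05, type 1 error 5 % (two-sided assumed), and "a minimal detectable difference of a 14 % absolute change, a standard deviation of 30 %, a correlation of 0.6 between baseline and follow-up measurement". **Assumption:** the spread of pharmacy sizes is not given, so the CV is taken from 0 to about 0.75.

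**1. The plan's own figure.** Design effect = 1 + 0.05 × (7 − 1) = 1.30, so the effective sample is 140 / 1.30 = 107.7.
- Baseline-adjusted SD = 30 × √(1 − 0.6²) = 24. Standard error = 24 × √(4 / 107.7) = 4.63, and 14 / 4.63 = 3.03. Power is 86 % with a normal reference and 81.6 % with t on 18 df. Six per pharmacy gives 77.1 % with t, so seven is the smallest number reaching 80 %.
- Change-score SD = 30 × √(2 × (1 − 0.6)) = 26.8. Power is 77 % with a normal reference and 72.6 % with t on 18 df.

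The stated 140 patients and 80 % power are thus reproduced, within 2 points, by a baseline-adjusted variance and a t reference on 18 df. The article does not say which variance or reference was used.

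**2. Exact size, unadjusted, equal pharmacies.** Let SS be the within-arm sum of squares of the 20 pharmacy means.
- Unbiased variance of the arm difference: (SS / 18) × (2 / 10) = SS / 90.
- Ordinary sandwich variance: SS / 10² = SS / 100.
- Ratio: 90 / 100 = 0.9.

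The true size of the nominal 5 % test therefore follows from the t distribution on 18 df and does not depend on the ICC:
- Ordinary sandwich, normal reference: P(|t18| > 1.96 × √0.9 = 1.859) = **7.9 %**.
- With the factor 20/19, normal reference: P(|t18| > 1.908) = 7.3 %.
- Ordinary sandwich, t18 reference: P(|t18| > 2.101 × √0.9 = 1.993) = 6.2 %.

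Width of the correct interval relative to the uncorrected one: 2.101 / 1.859 = 1.13.

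**3. Simulated size, Gaussian outcome, no treatment effect.** ICC 0.05, 12,000 to 20,000 trials per setting. The t reference has 20 − 2 − k df, with k the number of pharmacy-level covariates, each counted as one df.

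| k | CV | Ordinary, normal | Ordinary, t | Kauermann-Carroll, t | Mancl-DeRouen, t | Model-based, t |
|---|---|---|---|---|---|---|
| 0 | 0 | 8.1–8.2 % | 6.3–6.5 % | 5.2–5.3 % | 4.1–4.2 % | 4.9–5.0 % |
| 0 | 0.5 | 9.0–9.1 % | 6.9 % | 5.5 % | 4.2–4.3 % | 5.1–5.2 % |
| 0 | 0.75 | 9.9 % | 8.1 % | 6.2 % | 4.4 % | 5.9 % |
| 4 | 0 | 14.0 % | 10.9 % | 5.9 % | 2.5–2.6 % | 5.3 % |
| 4 | 0.5 | 15.2 % | 12.1 % | 6.2 % | 2.6 % | 5.8 % |
| 4 | 0.75 | 16.8 % | 13.9 % | 7.3 % | 2.8 % | 6.6 % |

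A separate run of a standard GEE routine at its default settings (1,000 trials per model) gave 8.1 % without and 14.5 % with the four covariates.

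**4. Sensitivity to the ICC (CV 0.5).** At ICC 0.01 and 0.10 the ordinary sandwich with a normal reference gives 8.7 % and 9.0 % unadjusted, and 14.7 % and 15.6 % with four covariates. The model-based t test is more sensitive: 3.7 % and 6.5 % unadjusted, 4.0 % and 7.8 % with four covariates. Kauermann-Carroll stays at 5.5 % to 5.9 % unadjusted and 6.0 % to 6.5 % with four.

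**The case against.** The strongest reply is that the article never says the robust errors are uncorrected and never names a normal reference. A Kauermann-Carroll or Mancl-DeRouen estimator is also a robust standard error, and a condensed article commonly leaves that choice to an analysis plan, which is not at hand. This stands to the extent that the figures must be conditional. A reader might infer that the trial's primary test will run at 8 % to 9 %; the document does not establish that. It does not dispose of the point, because the ordinary form is what the words most naturally mean, nothing in the text points to a correction, and a t reference alone still leaves an excess.

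Three further readings go too far:
- **That 14 % describes the primary test.** It belongs to the secondary adjusted analysis. The four pharmacy-level covariates are examples, so the article does not commit to entering all of them.
- **That every outcome is affected to this degree.** The calculations cover continuous outcomes. Proportions and utilization frequencies were not simulated.
- **That a mixed model and an exchangeable structure contradict each other.** With a Gaussian outcome and identity link, a random pharmacy intercept implies exchangeable correlation, and robust errors can be computed for a mixed model. The ambiguity has consequences only for the logit models.

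The remedies are also imperfect. At ICC 0.05 with seven per pharmacy, the between-pharmacy variance estimate is zero in about 23 % of trials, and the degrees of freedom then depend on the software. Model-based errors also give up protection against a misspecified variance. These are reasons to specify the remedy with care, not reasons to keep the sentence as it is.

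**Conclusion.** The point holds in conditional form. If robust standard errors are computed in the ordinary way with a normal reference, the nominal 5 % test of a continuous outcome has a true size of about 8 % with equal pharmacies, and about 9 % to 10 % with an assumed size CV of 0.5 to 0.75. A t18 reference alone leaves about 6 % to 8 %. In the secondary adjusted model with four one-df pharmacy covariates, the size is about 14 % (about 11 % with a t reference) at equal sizes, and higher with unequal sizes.

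These figures rest on 20 pharmacies, about 140 patients, a Gaussian outcome and no correction in an analysis plan; a correction there would remove most of the inflation. The number of pharmacies, the patients and the data collection are unaffected. A t test on 18 df still has 81.6 % power under the baseline-adjusted variance, though 72.6 % under a change-score variance.

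**What to change.** Replace the sentence on robust standard errors before the data are analyzed.

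- **Continuous outcomes, either:** a linear mixed model with a random pharmacy intercept, REML, model-based standard errors and Kenward-Roger or Satterthwaite degrees of freedom, stating what applies when the pharmacy variance is estimated as zero. The simulated sizes above used fixed df of 20 − 2 − k.
- **Or:** keep robust errors, but use a small-sample-corrected sandwich (for example Kauermann-Carroll) with a t reference on the number of pharmacies minus the cluster-level parameters: 18 unadjusted, 14 with four one-df covariates.
- **Binary outcomes:** state whether the model is a random-effects logistic model or GEE, since the odds ratios differ. If GEE, use the same corrected sandwich and t reference. The REML and Kenward-Roger recipe is for linear models and does not carry over.
- **Adjusted model:** keep the pharmacy-level covariates few and prespecified. Categorical ones such as type or location may use more than one df each. Mancl-DeRouen becomes conservative with four (about 2.5 % to 2.8 %).

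The cost is a change of wording and a software option. Unadjusted intervals become about 13 % wider than the ordinary robust ones; no extra patients or data are needed.
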